## Abstract

**Background:**

Depression is a common condition whose first onset is usually in late adolescence or early adulthood. Internet-based interventions are an effective treatment approach to depression. The aim of this study is to investigate the effectiveness of a Dutch online cognitive-behavioural group course known as Master Your Mood (*Grip op Je Dip*) for young people reporting depressive symptoms. Secondary research questions involve maintenance of effect at 6 months, mediators, and predictors of better outcomes.

**Methods:**

We will conduct a randomised controlled trial (RCT) in which 244 young people aged 16-25 are randomly allocated to the Grip op Je Dip (GOJD) online group course or to a waiting list control group. The participants will be recruited from the general population. The primary outcome measure will be the severity of depressive symptoms according to the Center for Epidemiological Studies Depression Scale (CES-D). Other outcomes will include anxiety (Hospital Anxiety and Depression Scale-Anxiety, HADS) and mastery (Mastery Scale). Assessments will take place in both groups at baseline and three months later. Effect maintenance will be studied in the GOJD group six months after baseline, with missing data imputed using the expectation-maximisation method. Mediators and predictors of better outcomes will also be identified.

**Discussion:**

The trial should add to the body of knowledge on the effectiveness of Internet-based interventions for depression. To our knowledge, this will be the first RCT on an online group intervention in this field.

**Trial registration:**

NTR1694

## Background

Depression is a common mental disorder among adolescents and young adults. One recent study found a 12-months prevalence of 6.7% of 18- to 25-year-olds [1]. First onset is usually in adolescence; by 18 years of age, up to one in every four adolescents has had at least one depressive episode ([2-4]. Depression early in life can have serious implications for individuals' school and professional careers [5]. Adolescent depression is associated with problems such as poor school performance, school absence and dropout [6], problematic relations with parents and peers [7], increased use of tobacco and alcohol [8] and suicidal behaviour [9].

Subclinical depression is also a common condition, with an estimated prevalence of 17% to 21% among Dutch adolescents [10,11]. It involves having some depressive symptoms which together do not meet the full DSM-IV criteria for major depression [12]. Subclinical depression has been found to be a strong predictor of the onset of major depressive disorder within the next year [13,14]. There are also indications that the psychosocial functional impairment of people with subclinical depression is comparable to that experienced by people diagnosed with major depression [15,16]. Beyond the personal suffering involved, both major and subthreshold depression impose significant economic burdens in terms of health care costs and production losses in paid and unpaid work [17,18].

In view of the high prevalence rates, the serious outcomes and the economic costs of depression, it is essential to intervene at an early stage. Yet young people are not inclined to seek professional help. They tend to deny or underestimate problems, question the benefits of help and fear stigmatisation [19]. And if they do seek help, they often encounter waiting lists [20].

Internet-based approaches may offer a solution for the stigmatisation problem, in that they provide anonymity and the opportunity to undergo the intervention in the privacy of home. Another benefit is to enable a reduction in contact hours between professionals and clients. This could help tackle the problem of waiting lists and shortages of therapists. Internet-based interventions, with or without professional support and mostly based on cognitive-behavioural principles, have been found effective in treating depression, with results comparable to traditional psychological approaches [21-24].

The current study will focus on one specific type of Internet-based intervention: a professionally facilitated, cognitive-behavioural group course designed for young people with symptoms of depression. The perceived advantages of online group sessions as compared to individual approaches are social support and mutual recognition by group members (though they remain anonymous to one another) and the reduction of professional contact hours per participant as compared to individual treatment with support [25]. Three earlier studies on online group courses in mental health care have found positive outcomes in pre-post measurements, although relatively high attrition rates were reported, a general problem in Internet interventions [26].

Despite the clear benefits of web-based interventions for depression and their availability for all age groups from about 13 onwards, there is a lack of outcome studies on adolescents [27,28]. Only two randomised controlled trials have been conducted on prevention programmes for depression and anxiety [29,30]. The Calear study found that a universal prevention programme was effective in reducing symptoms of anxiety and depression only in males. The Van Voorhees study showed that a web-based behavioural change programme in primary care, in combination with either motivational interviewing or brief advice, was associated with declines in depressed mood and in the likelihood of clinical depression symptom levels; in combination with motivational interviewing it reduced the likelihood of depressive episodes and hopelessness.

The primary aim of the study we describe here will be to evaluate the effectiveness of a web-based group course called Grip op Je Dip (Master Your Mood), designed for young people aged 16 to 25 with depressive symptoms, by comparing it to a waitlisted control group. Secondary aims concern effect maintenance and potential predictors of positive outcomes. The present article describes and discusses the study design.

## Methods

### Study design

We will conduct a randomised controlled trial with two parallel groups: the GOJD online course group versus a waiting list control group. Ethical approval has been granted by an independent medical ethics committee (CCMO no. NL18984.097.07).

### Participating mental health care agencies

A total of 10 mental health care agencies have agreed to participate in the project. In providing the online GOJD course, all agencies work at a nationwide level with participants from all over the Netherlands.

### Sample

The sample is to consist of 242 young people aged 16-25 with mild to moderate depressive symptoms. The inclusion criteria are as follow: age 16 to 25, informed consent (including parental consent if aged 16 or 17) and a CES-D depression score from 10 to 45. The CES-D cut-off score for clinical depression is 16 [31] for adults, and for adolescents it is either 22 [32] or 24 [33]. For subclinical depression, no CES-D cut-off scores have been determined, but we have set the lower limit at 10 for this study. Applicants will be excluded if there are indications of suicidal ideation with intent and plan as assessed with the MINI-International Neuropsychiatric Interview (MINI-Plus) [34,35]. MINI-Plus assessment is mandatory for individuals with CES-D scores higher than 24; the MINI-Plus will be administered online in the chatroom.

### Recruitment

Participants will be recruited in the general population through advertisements in local and national newspapers, banners on websites, and leaflets provided in doctors' offices, mental health agencies and schools. Interested young people may apply for participation by completing a screening questionnaire on the website http://www.gripopjedip.nl. Those with CES-D scores between 10 and 45 will receive additional information about the study, an informed consent form and a baseline questionnaire. For those aged 16 or 17, parental consent is also required. Those with scores between 25 and 45 will be invited for an online session to assess suicidal ideation and plan using the MINI-Plus interview. Once judged eligible for the GOJD course, applicants will be randomly allocated to the course group or the waitlisted group (3 months).

### Randomisation

Randomisation will take place after completion of the screening procedure, informed consent statement and baseline questionnaire before the start of the course. Random allocation will be generated automatically by an online computer program so it cannot be influenced by course facilitators or researchers. A blocked randomisation scheme will be used (blocks of two), stratified by depressive symptoms (scores 10-24 versus 25-45) and age (younger than 18 versus 18 or older). These allocation sequences will be unknown to the course facilitators who are pushing the randomization button. Participants will be informed of their allocation by email and will receive a tailored referral if declined. Course participants will also receive a log-in code and homework for the first session.

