### Conditions: the intervention

The GOJD online course derives from the face-to-face intervention of the same name developed by the Trimbos Institute (Netherlands Institute for Mental Health and Addiction). That intervention was based on the Dutch version of the Coping with Depression Course [36]. The face-to-face course was adapted to the Internet in a collaborative effort involving the Trimbos Institute and three mental health institutions [37].

The resulting online GOJD group course is a structured, psychoeducational form of cognitive-behavioural therapy for depression. The core focus is the cognitive restructuring of thinking patterns. Course participants are encouraged to detect their own unproductive, unrealistic thoughts, and they are then taught to transform these into realistic, helpful thoughts. Performance of pleasant daily activities is also encouraged, and a mood measure is filled in daily to help understand the connection between pleasant activities and mood level. The course is given in a secured chatroom that is part of the website http://www.gripopjedip.nl, which also provides information and video films about depression. Participants' anonymity is guaranteed by a self-chosen nickname. Only a mobile phone number must be given to facilitators for sending pre-session SMS reminders. The course makes use of text and figures, smileys to express feelings in written texts, and home exercises.

GOJD consists of six 90-minute sessions, conducted at a fixed time once a week. The course is facilitated by one or two trained mental health promotion workers, depending on group size (a maximum of 6) and their experience in conducting online courses. Facilitators receive two days' prior training in the technical and therapeutic conduct of the course and in administering the online MINI-Plus interview.

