## Discussion

The study described here is a randomised controlled trial in which young people aged 16 to 25 with depressive symptoms will take the GOJD (Master Your Mood) online group course; the outcomes will be compared to those of a waiting list control group. The primary aim is to assess the effectiveness of the online course in terms of severity of depressive symptoms. Secondary aims are to study effect maintenance and to identify predictors of positive outcomes.

Internet-based interventions are known to be effective in addressing depression. By virtue of their anonymity and the reduced need for contact between participants and professionals, they hold promise to reach many individuals who need them. In the field of web-based interventions for depression, studies with young people are still scarce, as are studies on online group courses. This trial should add to the body of knowledge on the effectiveness of such interventions. We shall now discuss some methodological issues in the current trial.

A strong feature of the current trial is that the recruitment and screening of participants and the inclusion and exclusion criteria are similar to the usual procedures in mental health agencies. This should enhance the external validity of the results. The main differences between the study and routine care are the randomisation and the informed consent required for the study. In addition, in routine care, participants with CES-D scores higher than 45 may be allowed to participate in the course, if only in exceptional cases in pressing circumstances and under specific conditions.

One limitation of the study concerns the impossibility of comparing the GOJD outcomes with those of the waitlisted group at the six-month follow-up, since the latter will receive access to the course three months after baseline. This means that the longer-term effectiveness of the course cannot be assessed in this study. We will, however, study effect preservation at six months in the GOJD group. Another study limitation is that the blinding of participants to experimental conditions is not feasible, because of the behavioural nature of the intervention.

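### Fixed blocks of two, triggered by the facilitators who run the course, put allocation concealment at risk, and the assurance that allocation cannot be influenced goes further than the design secures

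*Protocol article*

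**What the plan says.** The Randomisation section sets the rule: "A blocked randomisation scheme will be used (blocks of two), stratified by depressive symptoms (scores 10-24 versus 25-45) and age". Two CES-D bands and two age bands give four strata. Agency is not a stratification factor, although ten agencies take part (Participating mental health care agencies).

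The same section gives two assurances. An online program generates the allocation "so it cannot be influenced by course facilitators or researchers". It adds: "These allocation sequences will be unknown to the course facilitators who are pushing the randomization button". On timing it says: "Randomisation will take place after completion of the screening procedure, informed consent statement and baseline questionnaire before the start of the course".

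The people at the button have other roles. Under Conditions: the intervention, facilitators lead the chatroom sessions and are trained in "therapeutic conduct of the course and in administering the online MINI-Plus interview". Under Sample, the MINI-Plus is mandatory above a CES-D score of 24 and can exclude an applicant. The trial is open: the Discussion says that "the blinding of participants to experimental conditions is not feasible, because of the behavioural nature of the intervention". The primary outcome, the CES-D, is self-rated.

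**The concern.** Concealment requires that whoever enters the next applicant cannot foresee the next arm. Not showing someone the list is only part of that; the arm must also not be deducible from what has already happened. A fixed block of two is the easiest pattern to deduce, because one visible allocation gives away its partner. Here the person entering applicants also delivers the course, so learns who was allocated to it, and may have interviewed some applicants beforehand.

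At stake is the primary comparison. If facilitators can sometimes foresee the next arm, more promising applicants could be entered when the course is due. The arms would then differ in prognosis before treatment, on an outcome that participants rate themselves. The article itself treats motivation as a possible predictor of outcome (Statistical analyses).

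**Working it through.** **Inputs.** Block size 2, four strata, facilitators at the button (Randomisation); 10 agencies (Participating mental health care agencies); 121 per condition, so 1:1 (Sample size). The article does not say which past allocations a facilitator sees, or whether facilitators are told the block size.

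**The plan's own figure.** The article gives no figure for predictability. Its only computed design figure is the sample size: n per arm = 2 × (1.645 + 0.842)² / 0.32² = 2 × 6.185 / 0.1024 = 120.8, so 121 per arm and 242 in total. This reproduces, and nothing below changes it.

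**Blocks of two, whole stratum visible.** The first allocation in a block is a coin toss and the second is its opposite.
- Determined share = 1/2 = 50%.
- Correct guesses = (0.5 + 1)/2 = 75%.

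Always guessing the opposite of the last allocation achieves the 75% even without knowing where blocks begin. Knowing the boundary adds certainty about which guesses are safe.

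**Blocks of two, partial view.** Assume one list per stratum shared equally by K agencies, with each facilitator seeing only their own agency's allocations. The previous allocation in the stratum is then visible with probability p = 1/K. The second place in a block is guessed correctly with probability p × 1 + (1 − p) × 0.5, and the first with 0.5. The average is 0.5 + p/4. A simulation of 4,000 sequences of 60 agrees:

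| K | 0.5 + p/4 | Simulated |
|---|---|---|
| 1 | 75.0% | 74.9% |
| 2 | 62.5% | 62.7% |
| 5 | 55.0% | 55.1% |
| 10 | 52.5% | 52.6% |

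**Larger blocks, whole stratum visible.** The fixed sizes come from enumerating all permuted blocks and guessing the under-represented arm. The determined share follows 2/(b + 2) for block size b.

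| Scheme | Determined | Guessed correctly |
|---|---|---|
| Fixed 2 | 50.0% | 75.0% |
| Fixed 4 | 33.3% | 70.8% |
| Fixed 6 | 25.0% | 68.3% |
| Fixed 8 | 20.0% | 66.6% |
| Random 4/6/8 | at most about 25% | about 67.7% (simulated) |

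For the mixed scheme, if the sizes were known, the determined share would be (4 × 1/3 + 6 × 1/4 + 8 × 1/5)/(4 + 6 + 8) = 4.43/18 = 24.6%. With undisclosed sizes it is lower.

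**Where choice remains.** Randomisation follows screening, consent and baseline, so the main freedom left is the order or timing of button presses. In the two strata with scores 25-45 there is also some judgement in the MINI-Plus. In the 10-24 strata the article makes no such interview mandatory.

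**The case against.** The strongest reply is that prediction needs sight of the preceding allocation in the same stratum, and the article does not say that facilitators have it. Participants learn their arm by email, the program holds the list, and recruitment is spread over ten agencies that all work nationwide. With a list shared equally and sight of one's own agency only, the gain over chance is about 2.5 percentage points. This stands. It is why the result must be given as a range, and why a reader who infers that concealment is defeated, or that every second allocation is in practice known, goes beyond the article.

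A reader might also infer that facilitators randomise several applicants in one sitting to fill a group, where a run within one stratum would expose the second of each pair. Nothing in the article describes this. It is possible, but cannot be assumed.

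Entry rests on a self-completed score, and the stated purpose of the MINI-Plus is to detect suicidal ideation with intent and plan, not to judge suitability. This narrows the scope for selection without closing it.

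Finally, it is tempting to say that no analysis could repair the bias. That is too absolute. Motivation is measured at baseline with four NML-P subscales, and baseline comparability is to be tested, so steering on measured traits could be partly detected and adjusted for. Steering on unmeasured traits could not.

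The reply does not rescue the stated assurance. An unknown list does not stop deduction from past allocations, and low visibility cannot be relied on when the article does not state it.

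**Conclusion.** The concern holds as a risk to concealment. That half of the allocations in each stratum are determined by the one before is exact, given fixed blocks of two at 1:1. How far facilitators could exploit this is uncertain: about 52.5% correct guesses under the ten-equal-agencies assumption, up to 75% with sight of a whole stratum. The article does not allow a choice between these ends, and it gives no evidence that steering would occur. What can be said firmly is that the Randomisation section claims more protection than its own scheme provides, in an open trial with a self-rated primary outcome. An avoidable risk with a cheap remedy should be removed.

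**What to change.** Replace the fixed blocks of two with randomly varying block sizes, for example 4, 6 and 8, in the same four strata, and do not disclose the sizes to facilitators. In the Randomisation section, state which past allocations facilitators can see, and limit the claim that allocation cannot be influenced to what that supports.

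The gain should not be oversold. With full sight, guessing falls only from 75% to about 68%. The larger benefit is that an allocation can no longer be known for certain from the single one before it.

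The cost is a setting in the randomisation program and slightly more possible imbalance. With blocks of up to 8, the arms can differ by at most 4 in a stratum, against 1 now. If all four strata stopped at that extreme in the same direction, the split would be 129 to 113. The variance factor would be 1/129 + 1/113 = 0.01660 against 2/121 = 0.01653, which is about 0.2% on the standard error. The sample size stays at 242.

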### Conditions: the intervention

The GOJD online course derives from the face-to-face intervention of the same name developed by the Trimbos Institute (Netherlands Institute for Mental Health and Addiction). That intervention was based on the Dutch version of the Coping with Depression Course [36]. The face-to-face course was adapted to the Internet in a collaborative effort involving the Trimbos Institute and three mental health institutions [37].

The resulting online GOJD group course is a structured, psychoeducational form of cognitive-behavioural therapy for depression. The core focus is the cognitive restructuring of thinking patterns. Course participants are encouraged to detect their own unproductive, unrealistic thoughts, and they are then taught to transform these into realistic, helpful thoughts. Performance of pleasant daily activities is also encouraged, and a mood measure is filled in daily to help understand the connection between pleasant activities and mood level. The course is given in a secured chatroom that is part of the website http://www.gripopjedip.nl, which also provides information and video films about depression. Participants' anonymity is guaranteed by a self-chosen nickname. Only a mobile phone number must be given to facilitators for sending pre-session SMS reminders. The course makes use of text and figures, smileys to express feelings in written texts, and home exercises.

GOJD consists of six 90-minute sessions, conducted at a fixed time once a week. The course is facilitated by one or two trained mental health promotion workers, depending on group size (a maximum of 6) and their experience in conducting online courses. Facilitators receive two days' prior training in the technical and therapeutic conduct of the course and in administering the online MINI-Plus interview.

### Conditions: the waiting list

The wait listed group does not get an intervention. They are told by e-mail that they will receive an invitation to participate after the waiting period of 3 months.

### Support

After the screening procedure, the participants are in contact with the facilitator and the group members only during the weekly course sessions in the chatroom. They are allowed to seek additional help outside the course if they wish.

### Assessments

Assessments will take place before randomisation (t0), three months later (t1) and three months after t1 (t2). Participants in both groups will receive automated emails with invitations to complete online questionnaires. Subsequent email reminders will be sent five and ten days after the first invitation, if necessary. To encourage response, participants will receive 10 euros' compensation for completing the t1 questionnaire and 10 euros for the t2 questionnaire. If they complete both questionnaires, a 5-euro bonus will be added, totalling 25 euros.

